### Sample size and power analysis

The current study will sample approximately 3,000 shifts from up to 60 ticket inspectors employed by the three companies during a three to four months intervention period. As mentioned, our block-randomization design using work shifts, not individual inspectors, ensures that treatment and control observations are independent of inspector characteristics, effectively making the 3,000 shifts the sample unit [32].

Importantly, the sample size in the current study will provide very high statistical power to detect even small effects. A priori power analysis indicates that the planned sample size will yield 90% power to detect very small effect sizes (Cohen’s *f*^2^ = 0.003) in a regression model. Even under conservative assumptions of substantial attrition—such as 20% missing data due to loss of interest among inspectors who fail to complete the survey—the study is still expected to maintain 90% power to detect similarly small effects (Cohen’s *f*^2^ = 0.004).

Further data-structural and model-specification choices may reduce this power. For example, this could result from the use of cluster-robust standard errors to account for inspectors working in dyads, the imbalance in the number of observations across experimental conditions, or other anomalies that may arise during data collection. Nevertheless, given that our power calculations indicate the ability to detect even very small effects, it is unlikely that such factors will meaningfully compromise the overall capacity of the analyses to detect effects of a small magnitude.

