### Randomized controlled trials on body-worn camera effects

The development of body-worn cameras has led to a growing number of international studies examining their impact on frontline staff’s interactions with citizens, particularly in U.S.-based police–public encounters [10,11]. These studies have explored the camera’s effect on police use of force [12], number of arrests [13], citizen complaints [14], and officer exposure to violence [15]. While studies have looked beyond the policing context, these studies have typically not implemented randomized controlled trials to test the effect of cameras among groups such as prison and probation service staff [5] or ambulance crews [7].

Theoretically, cameras are expected to regulate behavior through a “deterrence effect” or “threat mechanism,” in which their presence signals a higher likelihood of apprehension or conviction, thereby encouraging behavioral compliance [16]. Further, cameras are assumed to promote self-awareness and socially desirable behavior, influencing both the person carrying the camera and the citizen [17].

Beyond deterrence and self-awareness, the camera’s effect may also operate through alternative mechanisms, such as perceptions of procedural justice or organizational practices of conflict management. For example, one study found that citizens reported higher perceived procedural justice in encounters with officers carrying a body-worn camera than in those without [18], which in turn could reduce citizen aggression and staff victimization risk. Additionally, attending to alternative pathways is important if cameras increase rather than decrease victimization. Such a finding could suggest that cameras are experienced as instruments of power display, potentially eliciting defensive or resistant responses from citizens and escalating interactions [19,20].

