#### Team-level.

Inspectors from Company 1 occasionally and Company 3 always work in pairs, potentially causing spillover effects from the expected benefits of wearing a camera to colleagues. This is accounted for in the survey by asking whether the inspector worked alone or together with a colleague during the shift. For inspectors from the subcompany hired by Company 3 who always work with two or three colleagues, the randomization and treatment are allocated at the dyad-team-level to prevent spillover effects.

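### The 90% power at f² = 0.003 is given without alpha or sidedness; a two-sided 5% test gives about 85%, and the unit count ignores team randomization of the guards

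*Protocol article*

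**What the plan says.** The section on sample size and power sets the base: "The current study will sample approximately 3,000 shifts from up to 60 ticket inspectors employed by the three companies". Because assignment is made shift by shift, it describes the design as "effectively making the 3,000 shifts the sample unit". It then claims: "A priori power analysis indicates that the planned sample size will yield 90% power to detect very small effect sizes", with f² = 0.003 as the effect size. For 20% missing data it adds that "the study is still expected to maintain 90% power to detect similarly small effects", now at f² = 0.004. Neither the significance level nor the sidedness of the test is given.

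The section goes on to concede that cluster-robust standard errors for dyads, or imbalance between conditions, may cost power. It judges a meaningful loss unlikely because the detectable effects are so small. It gives no figure for the loss.

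The Team-level section says of the Company 3 guards that "the randomization and treatment are allocated at the dyad-team-level to prevent spillover effects". The Intervention setting section gives 18 such guards, working in units of two or three. The Data analyses section specifies OLS with one predictor, the assignment indicator, and cluster-robust standard errors for dyads.

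**The concern.** Two things do not fit together.

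First, the printed power and effect sizes do not match a conventional two-sided 5% test of one coefficient, and no other test is declared. The article gives reasons to want a two-sided test. It reviews evidence that cameras can raise victimization, says that "attending to alternative pathways is important if cameras increase rather than decrease victimization", and the participant information warns that a camera could increase exposure to aggression. A one-sided test for reduction could not show that result.

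Second, guards in one team share one assignment, so their shifts are not separate randomized units. Counting all 3,000 shifts as the unit overstates the information they carry.

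What is at stake is the accuracy of a stated design property, and of the argument that uses it to set clustering and imbalance aside. If the power is quoted as printed, a null result would be read as somewhat more informative than it is.

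**Working it through.** **Inputs from the article.** N = 3,000 shifts; N = 2,400 after 20% missing (0.8 × 3,000); 1:1 allocation; one tested predictor; f² = 0.003 and 0.004; 18 guards among up to 60 inspectors; teams of 2 or 3.

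**Inputs not in the article (assumed).** Alpha 5%; guard share of shifts 18/60 = 30%, which requires all 18 to enrol and work as many shifts as the others; intra-team correlation (ICC) 0.05 to 1.

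**Step 1: trying to reproduce the printed figures.** The noncentrality is λ = f² × N, and power ≈ Φ(√λ − z). Exact noncentral F and t calculations agree with the values below.

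- N = 3,000, f² = 0.003: λ = 9 and √λ = 3. Two-sided: Φ(3 − 1.960) = 85.1%. One-sided: Φ(3 − 1.645) = 91.2%.
- N = 2,400, f² = 0.004: λ = 9.6 and √λ = 3.098. Two-sided: Φ(1.138) = 87.2%. One-sided: Φ(1.453) = 92.7%.

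**Step 2: f² detectable with 90% power** (exact calculation).

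| Test at 5% | N = 3,000 | N = 2,400 |
|---|---|---|
| Two-sided | 0.003505 | 0.00438 |
| One-sided | 0.00286 | 0.00357 |

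The one-sided values round to the printed 0.003 and 0.004. The two-sided values would both round to 0.004; they give the printed pair only if the first is truncated. With a two-sided test, 90% power at f² = 0.003 needs about 3,504 shifts.

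**Step 3: team randomization (illustration only).** With team size m, the design effect for guard-shifts is DE = 1 + (m − 1) × ICC. With a 30% share, guards supply 900 shifts and the others 2,100.

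- Effective-N basis, Neff = 2,100 + 900/DE:
  - pairs, ICC 0.05: DE = 1.05, Neff = 2,957, two-sided power at f² = 0.003 is 84.6%
  - pairs, ICC 0.2: DE = 1.2, Neff = 2,850, power 83.2%
  - teams of three, ICC 1: DE = 3, Neff = 2,400, power 76.5%
- The effective-N basis presumes efficient weighting. For unweighted OLS, as planned, Neff = 3,000/(0.7 + 0.3 × DE):
  - pairs, ICC 0.05: Neff = 2,956, power 84.5%
  - teams of three, ICC 1: Neff = 3,000/1.6 = 1,875, power 65.9%

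The guard share matters too. For teams of three with ICC 1, the effective-N power is 79.7% at a 20% share and 72.8% at 40%.

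**Step 4: does the broader conclusion survive?** Take the worst OLS case above and remove a further 20%: 0.8 × 1,875 = 1,500. At f² = 0.01 (d = 2√0.01 = 0.20), λ = 15 and two-sided power ≈ Φ(3.873 − 1.960) = 97%. Effects of conventionally small size remain detectable.

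**The case against.** The best defence is that alpha and sidedness are simply not stated. The hypothesis is worded as a reduction, and a one-sided 5% test reproduces both printed f² values after rounding. The two-sided value for 3,000 shifts, 0.003505, also sits only just above the boundary for rounding to 0.003. This stands to the extent that a reader might infer the 90% is an outright arithmetic error, and the article does not establish that. It does not settle the point, because no one-sided test is declared and the article treats harm as a real possibility.

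The clustering loss is also disclosed: the power section names it, and cluster-robust standard errors are planned. That stands; only its size is missing. A reader might infer that team randomization brings power down to a definite figure around 80%. The article does not support that, since it gives neither the guards' share of shifts nor an ICC. Participation is voluntary and 60 is an upper limit. With pairs and ICC 0.05 the loss is about half a point.

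A reader might also infer that power is misstated for the badge comparison. The article presents that comparison as secondary and limited to two companies, and ties its power figures to the planned sample of about 3,000 shifts. It claims no power for the badge contrast, so there is nothing there to correct.

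Finally, for inspectors randomized individually, taking the shift as the unit of assignment is reasonable. The objection to the unit count concerns the team-randomized guards only.

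**Conclusion.** The point holds in limited form. The stated 90% power is not reproducible from what the article declares. Under a two-sided 5% test of one coefficient it is about 85% at f² = 0.003 with 3,000 shifts, and 87% at f² = 0.004 with 2,400. These two figures rest only on the assumed alpha and sidedness and need no clustering assumption.

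Treating all shifts as independent units conflicts with the team-level allocation of the guards. The size of that further loss is unknown: under the assumed 30% share it runs from negligible to roughly 9 points on an effective-N basis (85.1 − 76.5), and about 19 points for unweighted OLS at the extreme (85.1 − 65.9).

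Severity is low to moderate. Without clustering, the 90%-power effect moves from f² = 0.003 to 0.0035, or d from 0.110 to 0.118 (d = 2√f²), which is still very small. The trial's general ability to detect small effects is not in doubt.

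**What to change.** In the power section:

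1. State alpha = 5% and a two-sided test.
2. Restate 90% power as f² of about 0.0035 for 3,000 independent shifts and about 0.0044 for 2,400.
3. Count the guards' data by team-shift, and give power over a stated range of ICC and guard share, computed for the estimator actually planned.
4. Remove the statement that all 3,000 shifts are the sample unit, or limit it to inspectors randomized individually.
5. Base the remark that clustering is unlikely to matter on those figures.

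The cost is a few sentences and a short calculation. The figures become slightly less favourable. No change to recruitment, randomization or data collection is needed.

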### Field observations

In parallel with the rollout of the experiment, we will conduct field observations of inspectors’ work to gain an in-depth understanding of how cameras influence interactions between inspectors and passengers in practice. The primary aim is to explore the situated mechanisms that lead camera use either to have an effect or to have no effect. The fieldwork will involve one to two trained research assistants accompanying inspectors during their workdays. The number of observation days will be a minimum of 10 workdays, but the final total will be determined as the fieldwork progresses, depending on whether additional days yield new insights.

### Pilot feasibility study

Following good research practice for intervention studies [39], a pilot study was conducted in summer 2023 to explore the feasibility of testing the effect of body-worn cameras. The 20-day pilot tested block-randomizing body-worn camera-use across 83 work shifts for ten ticket inspectors employed by Company 3. To gain qualitative insight into inspectors’ attitudes and perceptions about cameras and the situational aspects of camera use, we also interviewed inspectors before the piloting phase and conducted field observations over two workdays where the inspectors wore cameras.

The pilot results showed that the randomized controlled trial is practically feasible, with minimal attrition and a well-functioning questionnaire capable of capturing even more subtle forms of victimization. Further, qualitative observations and interview material indicated that few passengers noticed the cameras, suggesting that further work is needed to test the role of camera visibility. See data from the pilot study at osf.io/tk5xq/.

### Ethics approval and consent

Intervention studies raise ethical questions, especially when the manipulation involves a principal risk that the individuals involved may be exposed to risks [37]. The study was approved by the Aalborg University Research Ethics Committee (Case No.: 2025-505-00488), and the pilot study was approved by the Department of Sociology’s Ethics Review Board at the University of Copenhagen (Case No.: 2022-0-2022-05).

Ethical procedures include voluntary participation based on written informed consent. As previously mentioned, the participant information sheet contains details on the study’s aim and expectation, the hypothetical risk of camera use, the purpose of personal data collection, anonymity, and an opt-out option without notification of the participant’s employer. Furthermore, the procedures involve obtaining informed consent about sharing personal information, providing the research team’s contact details to allow participants to raise concerns, and implementing a process to exclude participants who repeatedly express such concerns. A member of the project group must confirm that a participant has received the intended information about the study with a signature on each of the participant information sheets.

### Inclusivity in global research

Additional information regarding the ethical, cultural, and scientific considerations specific to inclusivity in global research is included in the Supporting Information File.

### Data management

All collected data will be stored securely in accordance with Aalborg University’s and the University of Copenhagen’s security regulations. Once data collection is complete, analyses will be conducted on a pseudonymized dataset without participants’ names to minimize unnecessary personal identification. The non-anonymized data will be stored separately on a secure server and accessed only if needed for data validation during the analysis phase. Upon project completion, all data will be fully anonymized to ensure the confidentiality of participants.

## Discussion

The adoption of body-worn cameras reflects two contrasting trends: growing implementation by organizations employing frontline workers, and a comparatively fragile evidence base underpinning this practice. This study aims to help close this gap by examining the preventive effect of body-worn cameras in the transportation sector, which—like many other frontline sectors—is experiencing rapid growth in the use of body-worn cameras as a safety technology. Specifically, by sampling Danish transportation inspectors, the study addresses the need for research conducted in contexts other than U.S. policing.

The study presents a robust experimental design with block-randomization at the shift level and survey-based measures of both perceived safety and victimization. The victimization measure spans from physical violence to verbal abuse and harassment—a common experience among transport staff but rarely captured in prior research, which has relied on official incident records. Additionally, we advance the literature by conducting a parallel field observational study, which sheds light on the situational mechanisms through which cameras may influence staff-passenger interactions.

Despite these strengths, limitations remain. First, camera practices vary across the three included companies, which may affect the comparability of treatment conditions. Second, our reliance on outcome measures collected through self-report from unblinded inspectors introduces a risk of expectancy bias, with inspectors potentially over- or underreporting victimization depending on their attitudes toward cameras. Third, the design does not safeguard against inspectors adapting their behavior based on treatment assignment or carrying learned behaviors from one condition to the other.

Accordingly, our study—like any single study—cannot definitively settle the question of whether body-worn cameras have a protective effect, underscoring the need for further replications and meta-analytical syntheses to evaluate the robustness and heterogeneity of effects across diverse contexts.
